## Abstract

**Background:**

Lifestyle interventions, including increase in physical activity and dietary counselling, have shown the ability to prevent type 2 diabetes (T2D) in high-risk state individuals, but the prevalence is still skyrocketing in Australia, in line with global prevalence. Currently, no medicines are approved by the Therapeutic Goods Administration in Australia for the management of prediabetes. Therefore, there is a need of developing a safer, biologically efficacious and cost-effective alternative for delaying the transition of individual health state from prediabetes into T2D. In the current trial we propose to evaluate the effects of curcumin and/or long-chain omega-3 polyunsaturated fatty acids on improving glycosylated haemoglobin as a primary outcome, along with secondary outcomes of glycaemic indices, lipid profile and inflammatory parameters.

**Methods/design:**

Eighty individuals diagnosed with prediabetes, aged between 30 and 70 years, will be randomly assigned to double placebo, curcumin alone, fish oil alone or double active groups according to a computer-generated randomisation sequence for 12 weeks. At baseline and post-intervention visits participants will be asked to provide blood samples and undergo body composition measurements. A blood sample is used for estimating glycaemic profiles, lipid profiles and inflammatory parameters (C-reactive protein, whole blood cell count, adiponectin, leptin, interleukin-6). The interim visit includes review on compliance with supplements based on capsule log and capsule count, adverse events and anthropometric measurements. In addition to these procedures, participants provide self-reported questionnaires on dietary intake (using a 3-day food record), a physical activity questionnaire and medical history.

**Discussion:**

This trial aims to determine whether curcumin and/or long-chain omega-3 polyunsaturated fatty acids affect surrogate markers of glycaemic control which is relevant to delaying T2D. To date 38 participants completed the trial. No changes have been made to the clinical protocol post recruitment. If successful, this trial will provide considerable evidence for performing a larger trial to investigate whether this combination can be administered for preventing or delaying the onset of T2D in high-risk individuals.

**Trial registration:**

ACTRN12615000559516, registered on 29 May 2015).

**Electronic supplementary material:**

The online version of this article (doi:10.1186/s13063-016-1702-9) contains supplementary material, which is available to authorized users.

## Background

Type 2 diabetes (T2D) is a chronic and noncommunicable metabolic disorder characterised by hyperglycaemia resulting from defective secretion and/or action of insulin. The prevalence of T2D has been increasing rapidly worldwide at an alarming rate due to over nutrition, physical inactivity, urbanisation (especially in developing countries) and genetic predisposition [1–4]. People with prediabetes, who are at a high risk of developing T2D, have intermediate glucose levels that are elevated but not high enough to be diagnosed as T2D. They are classed as having either impaired glucose tolerance (IGT), impaired fasting glucose (IFG) or both. In 2015, over 318 million people were living with prediabetes worldwide, and this number is expected to rise to 471 million by 2035 [5]. Five to ten percent of the individuals diagnosed with prediabetes continue to progress to overt T2D annually [6]. Despite its complex and heterogeneous nature, T2D often coexists with obesity, hypertension and dyslipidaemia which are also common features of ageing [7–10]. Recent advances in molecular biology have provided in-depth understanding of the mechanisms that are involved in the pathobiology of T2D highlighting the role of glucotoxicity, lipotoxicity, oxidative stress and endoplasmic reticulum stress [11–13]. An elevated level of subclinical inflammation for prolonged periods is believed to be the primary trigger preceding all of the above mechanisms [14]. These pathological mechanisms mediate a reduction in insulin-stimulated glucose uptake leading to insulin resistance. Insulin resistance, present throughout the prediabetic stage, acts as a conduit between the progression of the subclinical inflammatory state to T2D.

The presence of insulin resistance in prediabetes also modulates the risk of developing T2D, and individuals with combined IGT and IFG are at greater risk of developing T2D than those with IFG or IGT alone [6, 15]. Insulin resistance is prevalent in both the cases, but people with IFG have more hepatic insulin resistance and those with IGT have more skeletal muscle resistance with less effect on hepatic insulin sensitivity [16, 17]. Along with insulin resistance, beta-cell dysfunction is present in both IFG and IGT individuals. However, they differ in time of insulin secretion response during an oral glucose tolerance test (OGTT). Individuals with IGT have both impaired early and late insulin response, in contrast to IFG individuals where only early phase insulin response is impaired [16]. These observations indicate that insulin resistance and moderate beta-cell dysfunction is already present in individuals with IFG and IGT (prediabetes).

Diabetes prevention studies have found that lifestyle interventions aiming at weight reduction through dietary intake changes and increase in physical activity significantly reduce the risk of developing T2D [15, 18]. Lifestyle interventions resulting in weight loss also improved insulin sensitivity and beta-cell function [19–21]. However, maintaining weight loss and physical activity is very difficult over longer periods of time. Lack of compliance with these interventions is a barrier for effectiveness in halting the progression to T2D in high-risk individuals, indicating that dietary and lifestyle modifications alone are insufficient. As prediabetes is not a full-blown disease state, to date, there are no approved drugs for its management. Lack of compliance with lifestyle interventions and pharmacological agents highlights the necessity of safe and efficacious interventions for the management of prediabetes.

Subclinical inflammation, being the primary trigger for many pathological mechanisms in the development of T2D, anti-inflammatory bioactives, such as curcumin and long-chain omega-3 polyunsaturated fatty acids (LCn-3PUFA), appear to be an attractive strategy to delay the risk of developing T2D in individuals with prediabetes. These bioactive compounds influence multiple numbers of physiological mechanisms and have relatively higher safety profiles [22, 23]. These bioactives could provide beneficial effects in insulin resistance and T2D by the following pathways: (1) down-regulating inhibitor of kappa B kinase (IKK)/nuclear factor kappa B (NFκB), and c-Jun N-terminal kinase (JNK) pathways for lowering chronic low-grade inflammation, (2) scavenging reactive oxygen species (ROS) and reducing oxidative stress, (3) providing cytoprotection for improving beta-cell function, (4) reducing the accumulation of fatty acid metabolites for increasing insulin sensitivity, (5) up-regulation of 5' AMP-activated protein kinase (AMPK), and (6) modulating peroxisome proliferator-activated receptor gamma (PPARγ) agonistic activity.

Some preclinical studies have reported synergistic anti-inflammatory effects of curcumin and docosahexaenoic acid (DHA) combination. These observations suggest that curcumin might provide synergistic anti-inflammatory effects with LCn-3PUFA in the prevention of T2D [24–26]. In this study we aim to perform a 2 × 2 factorial, double-blinded, randomised placebo-controlled trial to evaluate the complimentary or synergistic effects of curcumin and/or LCn-3PUFA primarily on glycaemic profiles and in individuals with prediabetes (IFG, IGT or both). In addition to these parameters we are also measuring lipid profile and inflammatory parameters to determine the effects of curcumin and/or LCn-3PUFA on cardiovascular risk factors and chronic low-grade inflammation.

## Method/design

This is a 12-week 2 × 2 factorial, double-blinded (study investigator and participants), randomised placebo-controlled intervention trial for preventing or delaying the onset of T2D using curcumin and/or fish oil as supplements. Eighty individuals diagnosed with prediabetes (IFG fasting glucose 6.1–6.9 mmol/L; IGT-2 h OGTT plasma glucose ≥7.8 mmol/L and ≤11.1; glycosylated haemoglobin (HbA1c) 5.7–6.5 mmol/L) aged between 30 and 70 years will be screened for enrolment at two sites; Nutraceuticals Research Group (NRG) and John Hunter Hospital (JHH) in Newcastle, NSW, Australia. Potential participants who meet the inclusion and exclusion criteria will be randomised to receive double placebo (corn oil capsules or curcumin placebo tablets), curcumin plus placebo matching for fish oil, fish oil plus placebo matching for curcumin or both curcumin and fish oil. Participants visit the trial sites three times at baseline (0 weeks), interim (6 weeks) and post intervention (12 weeks). Figure 1 shows a flow chart of the study design and the Standard Protocol Items: Recommendations for Interventional Trials (SPIRIT) Checklist is presented as Additional file 1.

**Fig. 1 Fig1:**
[figure not shown]
Trial protocol flow chart

### Study aims

The primary aim is to evaluate the potential of curcumin and/or LCn-3PUFA for improvements in the HbA1c in individuals with prediabetes. Secondary outcomes include: fasting plasma glucose, insulin, fructosamine, insulin sensitivity (Homeostatic Model Assessment), lipid profile (total cholesterol (TC), triglycerides (TG), high-density lipoprotein cholesterol (HDL-C), low-density lipoprotein cholesterol (LDL-C)), C-reactive protein (CRP), interleukin (IL)-1β, IL-6, adiponectin and leptin. Erythrocyte fatty acid composition and plasma curcumin content are measured to determine compliance with the intervention.

### Inclusion criteria

To be eligible to participate in the trial, participants should be within the age range of 30–70 years. Their Body Mass Index (BMI) must lie between 25 and 45 kg/m^2^. They must be diagnosed either with IFG (fasting glucose 6.1–6.9 mmol/L), IGT (2-h OGTT plasma glucose ≥7.8 mmol/L and <11.1 mmol/L) or both. They can also take part in the trial if their HbA1c levels lie between 5.7 and 6.4% or they obtain a score of 12 or more in the Australian type 2 diabetes risk (AUSDRISK) tool assessment (a noninvasive questionnaire to determine the risk of developing diabetes). The participants should not take part in any clinical trial (particularly with new investigational drugs) before starting this trial. They must be readily available for 3 months and should be willing to maintain similar dietary patterns and physical activity during the trial period.

### Exclusion criteria

Participants are excluded if they are unwilling to provide blood samples during the initial and final visits. Based on the medical questionnaire they will also be excluded if they have established T2D, gall bladder problems, pacemaker implants, severe neurological diseases or seizures. Women who are pregnant or lactating will also be excluded. People who consume more than two servings of oily fish per week or take any other dietary supplements known to influence blood glucose levels are also ineligible to participate in the trial. Based on their medication intake from the medical questionnaire, participants will be excluded from the trial if they are taking aspirin, warfarin, clopidogrel, ibuprofen, naproxen, dalteparin, enoxaparin or heparin to avoid any possible drug interaction with curcumin.

### Sample size calculation

Based on the HbA1c data of the prediabetic people from other studies [27, 28], with a standard deviation of 0.5 units in HbA1c, a sample size of 17 participants in each treatment group will give 80% power to detect a 0.5-unit fall in HbA1c at a type 1 error (alpha) of 0.05. To allow for dropouts we will recruit 4 × 20 = 80 participants according to the inclusion criteria.

### Participant recruitment

Participants will be recruited from the Hunter region in NSW using media advertising and social media (Facebook and Twitter) approved by the University of Newcastle Media and Marketing Department. Recruitment flyers will be placed on notice boards at the University of Newcastle, local pharmacies, local pathology centres (with permission) and in newsletters. Participants will also be recruited from the Hunter Medical Research Institute (HMRI) Volunteer Register, as well as from clinics across John Hunter/Newcastle Community Health Centre and Belmont Hospital diabetes clinics, Medicare local and GP practice databases with consent from participating GPs. Interested participants will contact the study coordinator through email or telephone, who will screen the participants according to inclusion and exclusion criteria. Potential participants will receive a Participant Information Sheet and the Health, Diet (3-day food record) and Physical Activity Questionnaire (IPAQ long form) after telephone screening. Participants will return the completed questionnaires along with a signed Consent Form. Study investigators will use demographic and lifestyle details to determine participant suitability before visiting the NRG or JHH for a baseline visit.

### Baseline assessments

After returning their signed Consent Forms, participants are provided with baseline visit details (Table 1). They will need to complete a 3-day food record and physical activity (IPAQ) and medical questionnaires before visiting trial site. Participants will visit either NRG or JHH after a minimum of a 10-h overnight fasting. Baseline assessments include anthropometry measurements using bioelectric impedance and a 20-mL blood sample collection for assessment of plasma glucose levels, insulin, fructosamine, HbA1c, TC, TG, HDL-C, LDL-C, CRP, whole blood cell count (WBC), leptin, adiponectin and other inflammatory cytokines (IL-1β, IL-6).

**Table 1 Tab1:** Study timeline and trial assessments

Assessments				
Screening (telephone)	X			
Informed consent (mail)	X			
IPAQ questionnaire (mail)	X			
3-day food record (mail)	X			
Medical questionnaire (mail)	X			
		Week 1	Week 6	Week 12
		Baseline (visit1)	Test (visit 2)	Test (visit 3)
Randomisation		X		
Intervention allocation		X		
Anthropometry measurements		X	X	X
Blood sample		X		X
Food diary		X	X	X
Physical activity		X	X	X
Biochemical analysis		X		X
Fasting plasma glucose		X		X
Fasting plasma insulin		X		X
HbA1c		X		X
Fructosamine		X		X
HOMA IR, HOMA S, HOMA β, QUICKI		X		X
Total cholesterol		X		X
Triglycerides		X		X
HDL-C, LDL-C, Total/HDL-C ratio		X		X
CRP		X		X
Whole blood cell count		X		X
Il-6, Il-1β, adiponectin, leptin		X		X
Capsule count and log record			X	X
Plasma curcumin concentration				X
Erythrocyte fatty acids content		X		X
Adverse event reporting			X	X

*IPAQ* International Physical Activity Questionnaire, *HbA1c* glycosylated haemoglobin, *HOMA IR* Homeostatic Model Assessment for Insulin Resistance, *HOMA S* Insulin sensitivity, *HOMA β* beta-cell function, *QUICKI* Quantitative insulin Sensitivity Check Index, *HDL-C* high-density lipoprotein cholesterol, *LDL-C* low-density lipoprotein cholesterol, *CRP* C-reactive protein, *IL-6* interleukin-6, *IL-1β* interleukin-1 beta

### Randomisation

Eligible participants who attend the baseline visit are randomised into treatments with either double placebo, curcumin alone, fish oil alone or double active (curcumin and fish oil) groups according to a computer-generated randomisation sequence. This randomisation is done in equal block sizes of 8 to ensure the balance between equal numbers of men and women. Randomisation is carried out by an individual who is not involved in trial data collection and analysis. Investigational product will be carefully stored (under the responsibility of the investigator) in a locked, limited-access area, safe and separate from drugs. Only authorised persons will have access to the storage place and capsules will be stored in sealed HD-PE bottles at room temperature (15–25 °C) in a dry place, protected from light and away from heat sources. The active and placebo capsules are identical, encapsulated and matched for colour. To increase the compliance of participants to the intervention, they are provided with a capsule log sheet during the study period to record their capsule intake. At the end of the study they are advised to return the capsule containers along with their log sheet.

### Intervention

Following randomisation, participants will receive one of the following interventions:Placebo: 2 × 500-mg CN-Placebo capsules plus 2 × 1000-mg corn oil capsules per dayCurcumin (Meriva curcumin): 2 × 500-mg CN capsules (providing 180 mg curcumin/day) plus 2 × 1000-mg corn oil capsules per dayLCn-3PUFA (EPAX1050): 2 × 1000-mg fish oil (FO) capsules (providing 1.2 g eicosapentaenoic acid (EPA)/DHA) plus 2 × 500-mg CN-Placebo capsules per dayCombination (curcumin and LCn-3PUFA): 2 × 500-mg CN capsules (providing 180 mg curcumin/day) plus 2 × 1000-mg FO capsules per day (providing 1.2 g EPA/DHA)

The participants are advised to take four capsules daily (two with their morning meal and two with their evening meal) with no changes in their dietary intake or physical activity during the study period.

### Interim visit

Participants are scheduled for the interim visit after 6 weeks of the intervention period (Table 1). They will need to provide completed diet and physical activity questionnaires. Compliance for the intervention is measured by capsule count and capsule log sheet. The follow-up visit includes only a 10-h overnight fast and anthropometric assessments using bioelectric impedance. Any adverse events or reports of difficulties in compliance with the intervention are recorded during this visit.

### Post-intervention visit

The post-intervention visit is scheduled on the last day of the participant’s intervention period (Table 1). All baseline measures, including a 10-h overnight fast, anthropometric measurements and blood sample collection will be repeated on this visit. They will also be asked to fill out 3-day food record and physical activity questionnaires. Participants are advised to return capsule containers along with the capsule log sheet on the final visit day.

### Safety and compliance monitoring

During the follow-up and post-intervention visits, any serious adverse events (SAE), adverse events (AE) related to intervention, compliance with intervention, or issues with other procedures (e.g. blood collection, anthropometric measurements, etc.) are discussed with participants and recorded. The study coordinator will inform the principal investigator of all AEs and SAEs, who will then follow procedures for unblinding as necessary and notify the relevant bodies. Depending on the nature of AE or SAE, it may be necessary for treatment to cease and/or for the participant to be withdrawn from the study. Should the need for unblinding in the curcumin or LCn-3PUFA group versus placebo group arise, subjects may inform the study coordinator or anyone from the research team.

For emergency situations, subjects will be given an emergency contact card, which will provide general study information and contact information for the unbiased randomisers. Compliance of the participant to the intervention is measured using capsule count and capsule log record. Erythrocyte fatty acid analysis is used to measure participant compliance with fish oil. Serum levels of curcumin are measured using HPLC; this will be used as a measure to determine participant compliance with curcumin tablets.

### Ethics

This trial has been approved by the University of Newcastle and the Hunter New England Area Health Service Human Research Ethics Committees, Approval Nos. H-2014-0385 and HNE HREC 16/03/16/3.02, respectively. The trial is registered with the Australia New Zealand Clinical Trial Registry (Trial ID ACTRN12615000559516).

### Data collection and outcome measures

#### Primary outcome

The primary outcome measure in this trial is the difference in HbA1c levels in 12 weeks between double placebo, curcumin, LCn-3PUFA and double active groups from baseline to the post-intervention visit (Additional file 2). HbA1c is measured in blood samples obtained at baseline and post-intervention visits through the cation exchange HPLC method by Hunter New England Area Health Pathology Services (HNEHAPS) (accredited pathology laboratory for compliance with National Pathology Accreditation Advisory Council Standards).

#### Secondary outcomes

Secondary outcomes in this trial include glycaemic profiles and insulin sensitivity, Lipid profile and inflammation-related parameters (Additional file 2).

##### Glycaemic profiles and insulin sensitivity

In addition to primary outcome, we will also measure fasting glucose and insulin levels in serum samples obtained from the trial participants to evaluate the effects of curcumin and/or LCn-3PUFA on glycaemic control and insulin resistance between the four groups. These parameters will be measured by HNEHAPS. Insulin resistance will be calculated using the Homeostatic Model Assessment equations, HOMA IR (fasting insulin (U/L) × fasting glucose (mmol/L)/22.5). The beta-cell function will be measured using HOMA β (20 × fasting insulin (IU/ml)/fasting glucose (mmol/ml) − 3.5).

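### The HOMA β formula lacks its bracket and its units conflict with the HOMA IR formula beside it, so beta-cell function computed as printed is wrong and can be negative for every participant

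*Protocol article*

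**What the plan says.** The section Glycaemic profiles and insulin sensitivity, under Secondary outcomes, gives two formulas in consecutive sentences, both built on the same fasting insulin and fasting glucose results.

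- Insulin resistance: "HOMA IR (fasting insulin (U/L) × fasting glucose (mmol/L)/22.5".
- Beta-cell function: HOMA β as 20 × "fasting insulin (IU/ml)/fasting glucose (mmol/ml) − 3.5".

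The second is introduced with "The beta-cell function will be measured using HOMA β". Table 1 schedules "HOMA IR, HOMA S, HOMA β, QUICKI" at baseline and week 12, and HOMA β is the only item there labelled as beta-cell function. Elsewhere glucose is in mmol/L, for example "IFG (fasting glucose 6.1–6.9 mmol/L" in the Inclusion criteria. The article does not restate or correct the HOMA β formula anywhere else.

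**The concern.** There are two separate faults.

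**The bracket.** By ordinary operator order, the printed expression is (20 × insulin/glucose) − 3.5. The standard HOMA definition is 20 × insulin/(glucose − 3.5), with the constant as a glucose value in the denominator. The printed form also gives the constant no useful role: subtracted from the ratio, it cancels from every absolute change and every group difference, which leaves 20 × insulin/glucose.

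**The units.** Insulin is in U/L in one formula and IU/ml in the other. Glucose is in mmol/L in one and mmol/ml in the other. Each pair differs by a factor of 1000, and neither insulin unit is the mU/L (the same as µU/ml) for which the constants 20 and 22.5 are meant.

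A derivation coded from this text would return a wrong value for a scheduled secondary outcome. Improved beta-cell function is part of the article's rationale for both supplements, so the index will be read as evidence on mechanism.

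**Working it through.** The article reports no HOMA value, so there is no stated figure to reproduce. The check evaluates the formulas directly.

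**Inputs**

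- Formulas and units: as printed in Glycaemic profiles and insulin sensitivity.
- Fasting glucose: 6.1–6.9 mmol/L for impaired fasting glucose (Inclusion criteria). Participants may enter by other routes ("They can also take part in the trial if their HbA1c levels lie between 5.7 and 6.4"%), so 4.5 mmol/L is taken as an assumed low value.
- Fasting insulin: the article gives none. A range of 2–50 µIU/ml is assumed, with 10 and 12 as worked examples.

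**1. One participant: insulin 10 µIU/ml, glucose 6.0 mmol/L**

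| Version | Calculation | Result |
|---|---|---|
| Bracket, conventional units | 20 × 10/(6.0 − 3.5) | 80.0 |
| As printed, conventional units | 20 × 10/6.0 − 3.5 | 29.8 |
| As printed, printed units | 20 × 0.00001/0.006 − 3.5 | −3.47 |

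HOMA IR is 10 × 6.0/22.5 = 2.67 with insulin in mU/L, and 0.010 × 6.0/22.5 = 0.0027 with insulin in U/L as printed.

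**2. The plausible range, in the printed units**

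Over insulin 2–50 µIU/ml and glucose 4.5–6.9 mmol/L, HOMA β runs from −3.49 to −3.28: negative and almost constant. It is positive only if 20 × insulin/glucose exceeds 3.5, that is, if insulin exceeds 0.175 × glucose. In the printed units this means:

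- glucose 6.1: 0.175 × 0.0061 = 0.0010675 IU/ml, about 1068 µIU/ml
- glucose 6.9: 0.175 × 0.0069 = 0.0012075 IU/ml, about 1208 µIU/ml
- glucose 4.5: about 788 µIU/ml

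Using the HOMA IR units (U/L and mmol/L) in the HOMA β formula gives the same negative values, because the two factors of 1000 cancel in the ratio.

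**3. Correcting only one fault** (insulin 10 µIU/ml, glucose 6.5 mmol/L)

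- Both corrected: 20 × 10/(6.5 − 3.5) = 66.7.
- Bracket only, printed units kept: 20 × 0.00001/(0.0065 − 3.5) = −0.000057, still negative.
- Units only, bracket still missing: 20 × 10/6.5 − 3.5 = 27.3. This looks credible but is 59% too low (27.3/66.7 = 0.41).

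**4. Effect of the missing bracket on a treatment effect** (conventional units, assumed values)

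| Change | With bracket | As printed |
|---|---|---|
| Glucose 6.5 to 6.0, insulin 12 | 240/3.0 = 80 to 240/2.5 = 96 (+20%) | 240/6.5 − 3.5 = 33.4 to 240/6.0 − 3.5 = 36.5 (+9%) |
| Insulin 10 to 12, glucose 6.0 | 80 to 96 (+20%) | 29.8 to 36.5 (+22%) |
| Glucose 6.5 to 6.0 and insulin 12 to 10.5 | 80 to 210/2.5 = 84 (rise) | 33.4 to 210/6.0 − 3.5 = 31.5 (fall) |

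The printed form gives glucose too little weight relative to insulin. The distortion is large when glucose moves and small when only insulin moves. When both fall, the direction can reverse.

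**The case against.** The strongest case is that this is a typographical slip of little consequence. Several parts of that case are sound.

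- Negative values for everyone come from the printed units, not from the bracket alone. In µIU/ml and mmol/L the printed form is negative only below about 1.1–1.2 µIU/ml at glucose 6.1–6.9 (0.175 × 6.1 = 1.07; 0.175 × 6.9 = 1.21). An analyst who saw nearly −3.5 for everyone would look again.
- The HOMA IR unit error only rescales. Percentage changes, F statistics and P values are unchanged.
- The attenuation from 20% to 9% belongs to one example in which only glucose moves.
- The list of secondary outcomes in Study aims names insulin sensitivity but not beta-cell function, and HOMA β can be recomputed at any time from stored insulin and glucose results.
- The bracketed form comes from the standard definition of the index, since the article does not print it elsewhere.

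These points limit the weight of the error but do not remove it. The method is named and its definition is standard. The unit conflict can be seen from the article alone, and the negative result follows from the printed formula at any plausible insulin.

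Text extraction is not an adequate explanation. A lost µ might account for IU/ml, although the Greek letter in HOMA β survived in the same sentence. It cannot account for mmol/ml or for the missing bracket. Even µIU/ml with mmol/ml fails: insulin 10 and glucose 6.5 give about 30,766 without the bracket and −57 with it.

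The more serious risk is a partial repair. Someone who corrects the units and leaves the bracket out gets values that raise no alarm. Nor is this detail left to a fuller document, because the article states the formula and states it wrongly.

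**Conclusion.** The concern holds. As printed, HOMA β is wrong in form and in units, and the two HOMA formulas contradict each other on the units of the same measurements. In the printed units, HOMA β is −3.49 to −3.28 for every combination of insulin 2–50 µIU/ml and glucose 4.5–6.9 mmol/L. In conventional units without the bracket, it is 29.8 where the standard index is 80.0 (insulin 10, glucose 6.0), and the size and sometimes the direction of a change are altered.

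The insulin values, the glucose value of 4.5 and the pre–post changes are assumptions. The bracket rests on the standard HOMA definition. The fault is confined to derived secondary measures: HbA1c and the sample size are untouched. It should be corrected before the HOMA results are derived, but it does not threaten the trial's main conclusion. Whether the actual code repeats the error cannot be told from the article.

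**What to change.** Replace both formulas, using one set of units:

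- HOMA IR = fasting insulin (mU/L) × fasting glucose (mmol/L)/22.5
- HOMA β = 20 × fasting insulin (mU/L)/(fasting glucose (mmol/L) − 3.5)

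State that mU/L equals µU/ml, and confirm the unit in which the pathology laboratory reports insulin. Check the derivation code on one worked example: insulin 10 mU/L and glucose 6.0 mmol/L must return HOMA IR 2.67 and HOMA β 80.0.

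The cost is one line of text and a short check of the code. No new data are needed, because both indices derive from measurements already scheduled.
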